### Stakeholder involvement and ethics

A Stakeholder Involvement and Ethics Group will be responsible for working across the trial, economic and process evaluations. We recognise that pregnant teenagers are a vulnerable group, at greater risk of social exclusion (e.g. from lower socioeconomic groups, care leavers). Consequently, various sensitive and practical issues need consideration prior to study commencement, for example, consent for those aged under 16 and procedures to be followed in the event of child safeguarding concerns. The Stakeholder Group will work to identify potential issues that may arise during the course of the trial and advise on their appropriate management. This will entail the development of a range of Stakeholder Groups to support the conduct of the trial through the various stages of development to completion.

The collaborative involvement of lay and professional people in the Stakeholder Groups will provide added value to the trial teams. Public contributors will be part of core trial management groups: Trial Steering Committee, the Stakeholder Management Group and the Independent Data Monitoring Committee. Reference groups, including young mothers, will be set up to advise on trial information materials, provide advice at the different stages of the trial, and contribute towards the design of the trial participant website.

#### Process evaluation

The process evaluation will aim to understand variations in the impact of the intervention and to contextualise findings [74]. Routine FNP monitoring data will be integrated with planned process evaluations using quantitative and qualitative methods [75].

### The process evaluation will examine

•fidelity to programme content and style of programme delivery, and to pre-set frequency and duration targets

•participants’ engagement and satisfaction with FNP

•impact of FNP roll-out as perceived by local stakeholders (FNP teams, Health Visitors, Midwives)

•wider contextual influences on programme implement-ation and outcomes

Fidelity targets for FNP visits prescribe time allocation for different content domains. In the UK, delivery of the programme is integrated with Motivational Interviewing (MI) [76] which forms part of the foundation of the FNP. Fidelity assessment will include audio-recording a sample of home visits for women at each site (n=216). Recordings will be assessed for consultation content and MI competencies using thematic content coding and a validated scale measuring adherence to Motivational Interviewing techniques [77]. Dose will be assessed by comparing FNP monitoring data against set performance metrics. Interviews with a sample of FNP clients (n=72) will assess intervention exposure; participants in the non-intervention arm of the trial will not be interviewed. Trial recruitment and retention will be assessed by examining sample characteristics and attrition rates and predictors.

Evaluation of context will focus on mapping existing universal services using questionnaires with key informants at each site and accessing national and local policy guidelines and commissioning briefs. Planned analysis of trial outcome data will explore differential programme impact across practitioners, sites and sample sub-groups.

Further contextual factors affecting implementation and potential wider roll-out will be explored in telephone interviews with FNP supervisors and focus groups with FNP teams and other local Stakeholders (Midwives, Health Visitors). Assessing contamination will form part of the structured telephone interviews with local stakeholders and the focus group discussions.

#### Health economics and modelling

Intervention effects will extend beyond the health sector, both within the timeframe of the trial and in the future. Therefore two components of work are required: one to explore the relative value of effects within the different sectors (health, social care, education, criminal justice) and another to consider the longer term extrapolation of trial results (i.e. over the lifetime of the child). To inform both of these, a literature review of economic outcomes within criminal justice and education literature will be conducted.

Valuation of effects: preference elicitation work will be undertaken in order to measure the relative values that members of the general public place on the different outcomes of the trial. Specifically, a discrete choice experiment and a best-worst scaling exercise will be conducted. This work will consider the trade-offs that people are prepared to make between benefits in the different sectors, which will inform the relative magnitude of benefits accruing to different sectors.

Economic extrapolation: the extrapolation exercise will seek to link the primary outcomes of the trial with longer term outcomes in health, education, employment and criminality extending to the childhood and adulthood of the index baby, and the mother. A literature review will be conducted to capture studies that examine the association between the short term primary outcomes, as measured in the trial, and the longer term outcomes. The inclusion of the studies will be done in stages, where cohort studies of longitudinal nature that enrolled participants at birth stage or prenatally and were conducted in the UK will be prioritised. The results of the literature review will be summarized in a narrative way and all the links will be presented in a tabulated format. The results of the review will be interpreted in light of the FNP trial results.

### Statistical analysis

#### Main analysis – primary outcomes

The primary comparative analyses will be conducted on an intention-to-treat basis, with an emphasis placed on confidence intervals for differences between the randomised arms.

Descriptive statistics of demographic and outcome measures will be used to ascertain any marked imbalance between the arms at baseline. For birth weight and prenatal tobacco use at 34-36 weeks the primary comparative analyses will employ multivariable linear regression to investigate differences between the arms, adjusting for stratification/ minimisation variables. In the case of prenatal tobacco use the calibrated number of cigarettes per day reported at baseline will also be adjusted for. The result will be presented as the (adjusted) difference in mean number of cigarettes per day between the intervention and control arms. Parameter estimates will be shown alongside 95% confidence intervals (CIs) and p-values.

For the proportion of children with at least one emergency attendance and/or admission and proportion of women with known subsequent pregnancies, logistic regression will be used adjusting for stratification/minimisation variables. Comparisons will be presented as odds ratios, 95% CIs and p-values.

Multilevel modelling will be used to allow for clustering of effect within a site and Family Nurse. Where this analysis indicates little impact of clustering on effect then the results from the single level model will be presented. Sensitivity analyses will be conducted to investigate the potential impact of missing data, making different assumptions such as ‘best’ and ‘worst’ case scenarios as well as imputation models. Where variables exhibit marked imbalance at baseline, primary analyses will be repeated and adjustments will be made to check that this does not influence findings. The same analyses will be carried out for the secondary outcomes depending on the type of data.

Appropriate interaction terms will be entered into the primary regression analyses for each of the outcomes in order to conduct pre-specified subgroup analyses. These subgroups will be defined by the Trial Management Group in advance of any analysis being started with input from the trial team and summaries of current evidence from the literature. Since the trial is powered to detect overall differences between the arms rather than interactions of this kind, the results of these exploratory analyses will be presented using confidence intervals as well as p-values.

Routine data on compliance with the FNP and usual maternity and early childhood services will be collected and utilised in understanding any outcome differences between the two arms.

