### Sample size estimation

A total sample of 1418 for analysis will provide at least 90% power at the two-sided 2.5% alpha level to detect differences between the two arms of 10% (40% to 30%) in the proportion having any emergency attendance or emergency admission to hospital within two years, and of 7.5% (20% to 12.5%) in the proportion with a second pregnancy within two years. For each outcome measure, the expected improvement for the FNP arm relates to a small standardised difference (approx. 0.2 or odds ratio 0.6). This small standardised difference will enable us to detect effect towards the lower end of what we expect. We will allow for a pregnancy loss of 1.5%.

We expect to obtain follow-up data for three of the four primary outcomes on at least 90% of participants by accessing the medical records in hospital and primary care for both the mother and child. Follow-up smoking rates will be collected through the late pregnancy telephone interviews. We will therefore aim to recruit a total of 1600 pregnant women to achieve our target number for analysis, as this takes into account anticipated pregnancy loss and loss to follow up.

We have chosen to use a 2.5% alpha level to allow for multiple primary outcomes within each individual population in the trial – i.e. there are two primary outcomes for the mother (smoking and second pregnancy) and two for the baby (birth weight and emergency attendances/admissions). This gives a 5% type 1 error rate for each population.

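### The 2.5% level set for each primary outcome is not carried through to the analysis section, which presents all four primary outcomes with 95% confidence intervals

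*Protocol article*

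**What the plan says.** Under Sample size estimation, the protocol article powers the trial "at the two-sided 2.5% alpha level" and gives the reason: "We have chosen to use a 2.5% alpha level to allow for multiple primary outcomes within each individual population in the trial". It counts the outcomes as follows: "there are two primary outcomes for the mother (smoking and second pregnancy) and two for the baby (birth weight and emergency attendances/admissions". It then states the consequence: "This gives a 5% type 1 error rate for each population". The 2.5% is thus a multiplicity allowance for the primary outcomes and not only an input to the sample size.

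Under Statistical analysis, Main analysis – primary outcomes, the article says that the primary comparisons are by intention to treat and that emphasis falls on interval estimates of the between-arm differences. For birth weight and prenatal tobacco use: "Parameter estimates will be shown alongside 95% confidence intervals (CIs) and p-values". For emergency attendance or admission and second pregnancy: "Comparisons will be presented as odds ratios, 95% CIs and p-values". That section does not repeat the 2.5% level, does not mention 97.5% intervals and does not say how intervals and p-values are to be read together. It extends the same analyses to the secondary outcomes, so the outcomes with a multiplicity allowance are presented no differently from those without one.

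**The concern.** A two-sided 95% interval excludes the null value when the matching test gives p<0.05; the interval that matches a 2.5% test is the 97.5% interval. The article chooses one level when it plans the primary comparisons and another when it says how they will be shown, and the second is where it places the emphasis.

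The mismatch matters in one zone: p between 0.025 and 0.05. There the emphasised interval suggests an effect, while the result misses the level chosen to protect the trial against having two primary outcomes per population. The Discussion presents the trial as an evaluation of government policy, so headline intervals are likely to be read by people who will not return to the sample size section. Leaving the reading open also leaves a choice to be made after a borderline result is known.

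**Working it through.** **Inputs from the article.** Two-sided alpha 0.025 per primary outcome; two primary outcomes per population; stated error 5% per population; 1418 analysed and 1600 recruited; pregnancy loss 1.5%; follow-up at least 90% for three of the four outcomes; planned effects 40% to 30% and 20% to 12.5%; 95% intervals for all four outcomes. **Assumed, not stated in the article:** 1:1 allocation (709 per arm) and the correlation between outcomes.

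**1. The plan's own figures reproduce.**
- Error per population at 2.5% each: bound 2 × 0.025 = 0.05. Under independence, 1 − 0.975² = 0.0494. The stated 5% is right.
- Numbers: 1600 × 0.985 × 0.90 = 1418.4, matching 1418.
- Power = Φ{[d√n − 2.241√(2p̄(1−p̄))] / √(p₁(1−p₁) + p₂(1−p₂))} with n = 709.
  - 40% v 30%: (2.663 − 1.512)/0.671 = 1.716, power 95.7%.
  - 20% v 12.5%: (1.997 − 1.169)/0.519 = 1.595, power 94.5%.

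  Both satisfy the claim of at least 90%, already at the 2.5% level.

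**2. What would follow if the 95% intervals were the decision rule.** Each comparison would then run at 0.05. The error per population is 1 − P(|Z₁| < c and |Z₂| < c) for bivariate normal statistics, with c = 1.960 (5%) or 2.241 (2.5%):

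| Assumed correlation | Read at 5% | Read at 2.5% |
|---|---|---|
| 0 | 9.75% | 4.94% |
| 0.3 | 9.5% | 4.8% |
| 0.5 | 9.1% | 4.6% |
| 0.8 | 7.8% | 4.0% |

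The bound whatever the correlation is 10% in the first case and 5% in the second.

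**3. What results fall in the gap.** Unadjusted risk differences, 709 per arm, SE = √[(p₁(1−p₁) + p₂(1−p₂))/709]:
- Second pregnancy 20% v 15.9%: difference 4.1 points, SE 2.04, z = 2.01, p = 0.044. 95% interval 0.1 to 8.1; 97.5% interval −0.5 to 8.7.
- Emergency attendance or admission 40% v 34.6%: difference 5.4 points, SE 2.56, z = 2.11, p = 0.035. 95% interval 0.4 to 10.4; 97.5% interval −0.3 to 11.1.

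These are 4.1/7.5 = 55% and 5.4/10 = 54% of the planned effects. They are illustrations, but not far-fetched ones.

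**4. What matching intervals would cost in width.** The ratio is 2.241/1.960 = 1.14, so 14% wider on the scale of the model (log odds for the binary outcomes). At the planned effects the half-width of the risk difference goes from 4.9 to 5.6 points (40% v 30%) and from 3.8 to 4.4 points (20% v 12.5%).

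**The case against.** The strongest reply is that type 1 error belongs to the decision rule and not to the coverage of a displayed interval. The only significance level in the article is 2.5%, it is given for multiplicity, and the analysis section never withdraws it. P-values are reported beside every primary interval, and comparing them with 0.025 holds the error at or below 5% per population. Emphasis on intervals can simply mean emphasis on size and precision of effect. A reader might infer that the 5% control has been lost, but that needs a rule under which a 95% interval excluding the null counts as success, and the article states no such rule. All of this stands, and it limits the point.

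A second reply is that a one-sentence decision rule is usual material for a statistical analysis plan, which is not shown here and may contain it. That holds for the rule itself. It does not dispose of the mismatch, because the article does not leave the interval level open: it fixes it at 95%, twice, against its own 2.5%.

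A reader might also be tempted to quote the error over all four outcomes: 1 − 0.95⁴ = 18.5%, against 1 − 0.975⁴ = 9.6% at the planned level. The article claims control only within each population, so neither figure contradicts anything it says.

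**Conclusion.** The inconsistency is real and certain on the text: a 2.5% level per primary outcome in planning, and 95% intervals for the same four outcomes in the emphasised presentation. Its practical reach is results with p between 0.025 and 0.05. The error of up to about 10% per population (9.75% under independence, less if the two outcomes are correlated) is conditional on conclusions being read from the 95% intervals, which the article neither says nor rules out. The planned sample size, the power and the choice of models are not in question; the power figures above assume equal allocation. This is a point of wording to settle before unblinding.

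**What to change.** In Main analysis – primary outcomes, do one of the following:
- present 97.5% confidence intervals for the four primary outcomes and state that a primary effect is concluded only if p<0.025; or
- keep 95% intervals for description, and state explicitly that primary inference compares the p-value with 0.025 and that a 95% interval excluding the null is not by itself a positive primary result.

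The first is cleaner, because the emphasised interval and the test then agree, provided both come from the same model. Keep 95% intervals for secondary and exploratory outcomes. The statistical analysis plan should carry the same sentence.

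The cost is wording in two documents and, under the first option, primary intervals about 14% wider. There is no cost in participants or power, since 1418 was already planned at 2.5%.

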NFP has been adapted for the UK where it is known as the Family Nurse Partnership (FNP) programme and is part of the Healthy Child Programme in England. Formal evaluation has demonstrated that FNP is deliverable and acceptable within the UK with some encouraging findings in terms of outcomes [47-49]. Although there is evidence of programme effectiveness in the US, there is no rigorous trial evidence for FNP in the UK, which has universal access to more comprehensive supportive care for young first-time mothers [24,25]. It is this evidence of short-term outcome effectiveness (up to the child’s second birthday) that will be generated by the Building Blocks trial.

The trial is supported by a partnership between government, research and primary and secondary care teams. In 2008, Primary Care Trusts (PCTs) in England tendered to the Department of Health to provide the FNP programme within the study context. The successful 18 PCTs subsequently employed the FNP teams to deliver the programme. The Department of Health based FNP central team will provide FNP materials, training and ongoing support to the PCT local teams and maintain a central database of FNP activity.

FNP teams are comprised of up to eight nurses, each of whom carries a maximum caseload of 25 clients, a supervisor who carries a reduced caseload, and an administrator. This is similar to the NFP programme.

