## Methods

### Trial design

This trial is an individually randomised controlled trial with a parallel economic modelling study. Trial participants ***either*** receive usual universal services ***or*** usual universal services along with regular visits from trained Family Nurses (FN) from early pregnancy (of their first child) until the child is two years old, following a prescribed programme.

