### Intervention

#### FNP

Participants in the intervention arm will receive up to 64 home based visits from the FNP nurse during their pregnancy and in the two years following childbirth. Fidelity requirements on programme recruitment and delivery are specified by the developers of the US programme (Table 3).

**Table 3 T3:** **FNP fidelity goals **[47,48,72]

**FNP fidelity goals**	**Criteria**
**Recruitment and enrolment**	• at least 60% enrolled before 16 weeks of pregnancy and 100% no later than 28 weeks
	• 100% of clients enrolled are first-time mothers
	• 100% of clients enrolled are 19 years or younger at LMP
	• 75% of eligible clients who are offered the programme are enrolled
	• each family nurse enrols 25 families (or pro rata) within 9 months of recruitment
**Attrition**	Clients leave the programme at no more than these rates:
	• cumulative programme attrition is 40% or less through to the child’s second birthday
	In detail:
	• 10% or less during the pregnancy phase
	• 20% or less during the infancy phase
	• 10% or less during toddlerhood
**Dosage**	Clients receive:
	• 80% or more of expected visits during pregnancy
	• 65% or more of expected visits during infancy
	• 60% or more of expected visits during toddlerhood
	On average, length of home visits is around 60 minutes

In the UK, the Family Nurse provides the FNP programme, alongside the usual maternity services during pregnancy and the neonatal period. From one month to two years after birth, the Family Nurse continues to provide the programme undertaking the role of the Health Visitor. Around the time of the child’s second birthday care is handed over to a Health Visitor, whose input will vary depending upon recognised need and local resources.

Family Nurses are recruited from existing registrants on the Nursing Midwifery Council of the UK, mainly from Health Visiting but also from Nursing and Midwifery. Training in delivery of the programme will be provided to the Family Nurses by the FNP central team.

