### Randomisation

Prior to recruitment of a trial participant, the Local Researcher will confirm that the local FNP team has spare capacity, consent will be obtained and the baseline assessments completed. The Local Researchers will use a remote randomisation service (automated telephone or web) provided by Bristol Randomised Trials Collaboration (BRTC) to allocate the woman to FNP or usual care. The Local Researcher will inform the FNP team of participants allocated to receive the programme. The FNP team will then take responsibility to enrol the woman into the programme and provide the intervention. For women allocated to usual care, the woman’s community midwife will be informed. All participants’ General Practitioners will be notified of their recruitment to the trial.

A randomisation algorithm will minimise by gestation at recruitment (<16 weeks/16 weeks+), smoking status at recruitment (smoker/non-smoker) and first language/preferred language (English/non-English) for each site with a probability of 0.8. Therefore a random element is retained, further reducing predictability of allocation. The trial statisticians and economists will be blinded to treatment allocation until analyses are complete.

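### The single-level result may replace the multilevel one after a look at the data, on a criterion (little impact on effect) that nurse clustering barely touches, because it acts mainly on the standard error

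*Protocol article*

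**What the plan says.** In the statistical analysis section, under the main analysis of primary outcomes, birth weight and prenatal tobacco use are analysed by linear regression. Emergency attendance or admission and second pregnancy are analysed by logistic regression. The primary comparison is by intention to treat, "with an emphasis placed on confidence intervals for differences between the randomised arms". Clustering is then addressed in two sentences: "Multilevel modelling will be used to allow for clustering of effect within a site and Family Nurse", followed by "Where this analysis indicates little impact of clustering on effect then the results from the single level model will be presented". The article does not say how large an impact counts as little, or whether effect means the point estimate, its interval or the ICC.

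Three other places bear on this:
- Trial design: "This trial is an individually randomised controlled trial with a parallel economic modelling study". Under Randomisation, allocation is minimised "for each site with a probability of 0.8", so each site can contribute women to both arms. Only the FNP arm has Family Nurses.
- Background: "FNP teams are comprised of up to eight nurses, each of whom carries a maximum caseload of 25 clients". The fidelity goals in Table 3 add that "each family nurse enrols 25 families (or pro rata) within 9 months of recruitment".
- Sample size estimation: "A total sample of 1418 for analysis will provide at least 90% power at the two-sided 2.5% alpha level". No allowance for clustering is mentioned there.

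The health economics section, by contrast, allows for clustering in both its complete-case and its imputed analysis, without any condition.

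**The concern.** Women who share a Family Nurse may have correlated outcomes. In an individually randomised trial with nurses in one arm only, that correlation adds variance to the FNP arm's mean. It has little systematic influence on the estimated difference. A rule that asks whether the effect moved will therefore tend to answer no, whether or not the standard error needed to grow. The rule can discard the clustering in the very trials where it matters.

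At stake are the interval and p-value of every primary outcome, and the 2.5% level that the sample size section chose so as to control error within mothers and within babies. Choosing the headline model after both fits are seen, with no threshold, also leaves room for discretion that the plan need not have.

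**Working it through.** **Inputs from the article.** 1418 women analysed, taken as 709 per arm (equal arms assumed); two-sided alpha 2.5%, so z = 2.2414; targets 40% v 30% and 20% v 12.5%, or about 0.2 SD; 18 sites, up to 8 nurses per team, at most 25 clients per nurse.

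**Assumed.** Nurse ICC 0.01 to 0.05, since none is given. FNP women analysed per nurse, m: at the low end 18 × 8 = 144 nurses, 709/144 = 4.9, about 5; at the high end 800 women in full caseloads of 25 need 32 nurses, 709/32 = 22.2, about 22.

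**1. The plan's own figure.** Power = Φ[(|p1 − p2| − z·s0)/s1], with s0² = 2p̄(1 − p̄)/709 and s1² = [p1(1 − p1) + p2(1 − p2)]/709.
- 40% v 30%: s0 = 0.02533, s1 = 0.02519; (0.100 − 0.0568)/0.02519 = 1.716; power 95.7%.
- 20% v 12.5%: s0 = 0.01959, s1 = 0.01949; (0.075 − 0.0439)/0.01949 = 1.595; power 94.5%.

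The claim of at least 90% is met without clustering. Also, 1600 × 0.90 × 0.985 = 1418.4, which is the stated analysis sample.

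**2. Level of the single-level test under nurse clustering.** FNP-arm design effect DE = 1 + (m − 1)·ICC. With control women unclustered, true SE / single-level SE = k = √[(1 + DE)/2]. True level = 2[1 − Φ(2.2414/k)]; coverage of a nominal 95% interval = 2Φ(1.96/k) − 1.

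| m | ICC | DE | k | True level (nominal 2.5%) | Coverage (nominal 95%) |
|---|---|---|---|---|---|
| 5 | 0.01 | 1.04 | 1.010 | 2.65% | 94.8% |
| 5 | 0.05 | 1.20 | 1.049 | 3.3% | 93.8% |
| 10 | 0.02 | 1.18 | 1.044 | 3.2% | 94.0% |
| 10 | 0.05 | 1.45 | 1.107 | 4.3% | 92.3% |
| 22 | 0.01 | 1.21 | 1.051 | 3.3% | 93.8% |
| 22 | 0.02 | 1.42 | 1.100 | 4.2% | 92.5% |
| 22 | 0.05 | 2.05 | 1.235 | 7.0% | 88.8% |

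**3. What the rule would select.** 4,000 null trials were simulated per setting: continuous outcome, 709 per arm, unequal caseloads, multilevel model with nurse variance in the FNP arm only. The rule was read literally: keep the single-level model if the estimate moves by less than 0.02 SD. That cut-off, 10% of the 0.2 SD target, is an assumption because the plan gives none. For ICC 0.01 to 0.05:
- The single-level model was kept in 99–100% of trials at m = 5, 96–100% at m = 10 and 86–99% at m = 20.
- The median shift in the estimate was 0.0004 to 0.008 SD, while the mean standard error rose by 2% to 23%.
- Rejection at nominal 2.5% under the rule was 2.6% (m = 5, ICC 0.01), 3.4% (m = 10, ICC 0.02), 5.4% (m = 10, ICC 0.05) and 7.0% (m = 20, ICC 0.05). Always using the multilevel model gave 2.3% to 3.1%. Simulation error near 2.5% is √(0.025 × 0.975/4000), about 0.25 percentage points.
- If the rule instead asked whether the standard error changed by less than 5%, rejection was 2.5% to 3.2%.

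**4. Logistic outcomes.** A nurse random intercept in the FNP arm moves the odds ratio from 0.643 to 0.639 (ICC 0.01) or 0.622 (ICC 0.05) for emergency attendance or admission, and from 0.571 to 0.564 or 0.536 for second pregnancy. The effect does move here, modestly.

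**5. Site.** With both arms in each site, the single-level SE is 1/√(1 − ICC) times the true one: 1.005 to 1.026 for site ICC 0.01 to 0.05. Dropping site errs on the cautious side, so the concern is with nurses only.

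**6. Power with nurse clustering.** Multiplying the FNP arm's variance by DE in step 1 gives, for emergency / second pregnancy, 93.8% / 92.3% (m = 5, ICC 0.05), 91.6% / 90.0% (DE 1.4) and 83.4% / 81.4% (m = 22, ICC 0.05).

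**The case against.** The strongest reply is that effect need not mean the point estimate alone. The same section stresses confidence intervals, so the sentence can be read as asking whether the estimate and its interval change. On that reading the rule does almost no harm, as the 5% standard-error version in the working shows. This stands as a limit on the claim. A reader might infer that the rule is bound to select intervals that are too narrow. The article does not support that: it needs a nurse ICC above zero and the literal reading. The text does not settle the reading, however, and sets no threshold under either.

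The high end of the range is also a ceiling. About 22 women per nurse means 32 nurses over 18 sites, fewer than two per team where teams may have eight. At 5 per nurse and ICC 0.01 the standard error is wrong by only 1%. Both points stand, although the enrolment goal in Table 3 keeps large caseloads possible.

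Two further inferences are tempting and fail. One is that the plan gives control women a nurse level. It does not; its wording is compatible with a nurse effect in the FNP arm only, and the exact specification may lie in an analysis plan not shown. The other is that the power statement is wrong. It reproduces at 95.7% and 94.5%.

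The objection does not remove the rule itself, which is stated and not merely left out.

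**Conclusion.** The concern holds in a limited form. The article states a data-driven choice of the primary model, without a threshold and on a criterion poorly matched to what nurse clustering does. Read literally, the rule can keep the single-level model when the standard error should grow, and in simulation it did so in at least 86% of trials at ICC 0.01 to 0.05.

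The true level of a nominal 2.5% test is then about 2.65% to 7.0%, and a nominal 95% interval covers about 94.8% down to 88.8%. The worst figures need full caseloads and ICC 0.05 together. These sizes rest on assumed ICCs, equal arms and 5 to 22 women per nurse. For the two logistic outcomes the odds ratio also shifts somewhat, so it is not exact to say that clustering leaves the effect alone.

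Power is a side issue. The stated 90% holds up to an FNP-arm design effect of about 1.4.

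**What to change.** Delete the conditional sentence. For all four primary outcomes, keep as primary the model that allows for nurse clustering in the FNP arm, whatever the estimated ICC:
- a nurse random effect in the FNP arm only, with control women, and FNP women who never have a nurse, as singletons;
- FNP women assigned to their first allocated nurse, so that later changes of nurse or leaving the programme do not alter the clusters and intention to treat is kept;
- site adjusted for as a stratification factor;
- the single-level result shown as a sensitivity analysis.

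Standard errors made robust to clustering by nurse, on the same definitions, would serve the same purpose. For the two logistic outcomes they leave the odds ratio on the scale of the single-level model, whereas a random intercept gives one conditional on nurse, so the plan should name which is reported.

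At most, add to the sample size section that the 90% assumes an FNP-arm design effect of no more than about 1.4.

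The cost is a change of wording and slightly wider intervals if nurse effects exist. No new data collection should be needed: the trial team will already access the database of Family Nurse visits, and the planned Family Nurse model presupposes that each woman can be linked to a nurse.
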